### Minimal sample size

2.3.

We did not calculate minimal sample size to achieve a given statistical power because this is an exploratory study (28, 29) and we are unaware of other studies with a similar design and purpose. Recent studies of the protective effects of precooling and curcumin on organ injury among patients with EHS included only 8–12 participants (30, 31). A study that examined immune cell dynamics during EHS was able to obtain statistically significant results using only 11 patients (32). Therefore, to differentiate the immune profiles, we aim to enroll at least 40 subjects in each of the four cohorts.

### Study protocol

2.4.

Specially trained investigators will screen individuals for potential inclusion based on the inclusion and exclusion criteria, and they will obtain written informed consent from the individuals or their legal representatives. The items to be measured are listed in Table 2. The following baseline data will be recorded from all participants on case report forms: age, sex, ethnicity, profession, education level, body mass index, history of smoking and drinking, family medical history, laboratory results, comorbidities, and treatments. Comorbidities include cardiovascular disease, hypertension, asthma, chronic obstructive pulmonary disease, epilepsy, stroke, diabetes, hyperthyroidism, hypothyroidism, chronic liver disease, virus infection, and neurological disease. Treatments include antihypertensive agents, aspirin, statins, anticoagulant drug, oral antidiabetic agents, insulin, and levothyroxine.

**Table 2 tab2:** Schedule of enrollment, intervention, and assessment.

Items	Screening	Post-allocation	1 month after trial
	Visit1 (Within 24 h of admission)	Visit2 (During hospitalization)	Visit3
Informed consent	**×**		
Inclusion/exclusion criteria	**×**		
Basic information^a^	**×**		
Smoking and drinking history	**×**		
Family medical history	**×**		
Comorbidities and treatments^b^	**×**		
The location of onset, symptoms and vital signs on admission (for heatstroke patients and sepsis patients)	**×**		
Preoperative data (for CPB patients)		**×**	
Intraoperative data (for CPB patients)		**×**	
Mechanical ventilation		**×**	
Renal replacement therapy		**×**	
Transfusion		**×**	
Usage of medication^c^		**×**	
Death			**×**
Infection			**×**
Complications^d^			**×**

a Age, gender, job, height, and weight, etc.

b Comorbidities include cardiovascular disease, hypertension, asthma, chronic obstructive pulmonary disease, epilepsy, stroke, diabetes, hyperthyroidism, hypothyroidism, chronic liver disease, virus infection, and neurological disease. Treatments include antihypertensive agents, aspirin, statins, anticoagulant drug, oral antidiabetic agents, insulin, and euthyrox.

c Including vasoactive agents, glucocorticoids, and antibiotics.

d Including cardiovascular, respiratory, nervous, digestive or urinary systems complications.

Additional information will be recorded onto case report forms for the three patient cohorts. In the case of heatstroke and sepsis patients, the location of onset, symptoms, and vital signs on admission will be collected. In the case of CPB patients, preoperative data will be recorded on surgical diagnosis, New York Heart Association cardiac function classification, and EuroSCORE II, as will intraoperative data about surgical procedure, surgery time, anesthesia time, amount of blood transfusion, urine output, and medicines used during surgery. We will record mechanical ventilation, renal replacement therapy, and transfusion, as well as use of vasoactive agents, glucocorticoids, and antibiotics during hospitalization for the three patient cohorts. These groups will be followed up at 30 days after admission, either in person if the individual remains in hospital or by telephone or WeChat if the individual has been discharged. During follow-up, data will be collected on death, infection, and complications affecting cardiovascular, respiratory, nervous, digestive, or urinary systems.

These data will be entered onto case report forms. To protect confidentiality, the files will be stored in a secure and locked place and manner, and the subject identification and private information will be deleted from all study documents. To control the quality of data, supervising investigators will be required to ensure the accuracy and completeness of the data. Then the data will be doubly entered into the EpiData 3.10 database system by two investigators. After finishing the data entry and dealing with the query, the database will be locked under the orders of the principal investigator. No one is allowed to view the database without authorization; otherwise, they should notify the principal investigator.

#### Blood collection

2.4.1.

Venous blood (10 mL) will be collected into tubes coated with ethylenediamine tetraacetic acid within 24 h after admission in the case of heatstroke and sepsis patients, at the end of CPB in the case of CPB patients, and during outpatient visits at the International Medical Center in the case of healthy controls.

Within 4 h after collection, 8 mL of the blood samples will be processed to isolate peripheral blood mononuclear cells (PBMCs; see section 2.4.2), while the remaining 2 mL of blood will be centrifuged at 100 *g* at 4°C for 5 min, and then 500 μL of plasma will be stored at −80°C for cytokine assays (see section 2.4.5).

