#### Assay of cytokine levels in plasma

2.4.4.

Plasma samples will be analyzed for the following cytokines using commercial ELISAs: perforin, granzyme B, granulocyte-macrophage colony-stimulating factor, high mobility group box-1, heat shock protein-72, tumor necrosis factor-α, interferon-γ as well as interleukins (ILs)-1α, 1β, 2, 4, 6, 10, and 21, which will be measured according to the manufacturer’s instructions. Calibration curves will also be prepared according to the manufacturer’s instructions. Absorbance at appropriate wavelengths will be measured using a microplate reader (39).

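### The 500 µL of plasma kept for 14 ELISA analytes leaves about 36 µL each, so the cytokine panel may run short; the same draw could supply more.

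*Protocol article*

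**What the plan says.** Section 2.4.1 of the protocol article draws 10 mL of venous blood per participant. Of this, 8 mL goes to cell preparation. The other 2 mL is spun, and "then 500 μL of plasma will be stored at −80°C for cytokine assays". Under section 2.4.2 the blood for cell preparation goes into red-cell lysis solution and the supernatant is thrown away, so its plasma is not kept.

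On the assays, section 2.4.4 states: "Plasma samples will be analyzed for the following cytokines using commercial ELISAs". The list has two parts: "perforin, granzyme B, granulocyte-macrophage colony-stimulating factor, high mobility group box-1, heat shock protein-72, tumor necrosis factor-α, interferon-γ" and "interleukins (ILs)-1α, 1β, 2, 4, 6, 10, and 21". The method is given only as "which will be measured according to the manufacturer’s instructions", with absorbance read on a microplate reader. Well volume, dilution, number of replicates and kit format are not stated.

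The abstract and the Introduction name the plasma cytokine comparison across the four cohorts as a component of the study. The abstract describes profiling at one time point, and section 2.4.1 describes one blood collection.

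**The concern.** The protocol fixes both sides of a budget, the plasma stored and the number of analytes to be measured from it, and does not show that they balance. An absorbance readout on a plate reader most naturally means conventional plate ELISA with one analyte per well. On that reading the 14 assays draw on one 500 µL pool.

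If the pool runs out, some analytes go unmeasured for some participants, or samples are diluted or run singly because of volume and not because the kit calls for it. In either case the cytokine comparison is incomplete or less precise, and the choice of what to drop is made at the bench. With a single draw, the missing volume cannot be recovered afterwards.

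**Working it through.** The protocol states no volume per assay and no total requirement, so there is no figure of its own to reproduce.

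**Inputs from the protocol**
- Plasma stored: 500 µL (section 2.4.1).
- Analytes (section 2.4.4): 7 non-interleukins (perforin, granzyme B, GM-CSF, HMGB-1, HSP-72, TNF-α, IFN-γ) + 7 interleukins (IL-1α, IL-1β, IL-2, IL-4, IL-6, IL-10, IL-21) = 14.

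**Supply per analyte**
- 500/14 = 35.7 µL undiluted.
- In duplicate: 35.7/2 = 17.9 µL per well.
- Neither figure allows for dead volume or a repeat run.

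**Need, with assumed kit parameters**

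Plasma needed = 14 × well volume × replicates ÷ dilution factor. Analytes covered = 500 ÷ (well volume × replicates ÷ dilution factor), rounded down and capped at 14. Well volume, replicates and dilution are all assumptions.

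| Well volume | Replicates | Dilution | Plasma needed | Within 500 µL? | Analytes covered |
|---|---|---|---|---|---|
| 25 µL | 1 | 1:2 | 175 µL | yes | 14 |
| 25 µL | 1 | none | 350 µL | yes | 14 |
| 25 µL | 2 | none | 700 µL | no | 10 |
| 50 µL | 1 | none | 700 µL | no | 10 |
| 50 µL | 2 | none | 1,400 µL | no | 5 |
| 100 µL | 1 | none | 1,400 µL | no | 5 |
| 100 µL | 2 | none | 2,800 µL | no | 2 |
| 50 µL | 1 | 1:2 | 350 µL | yes | 14 |
| 100 µL | 1 | 1:3 | 467 µL | yes | 14 |
| 100 µL | 2 | 1:5 | 560 µL | no | 12 |
| 100 µL | 2 | 1:6 | 467 µL | yes | 14 |

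**Break-even dilution, if uniform across the panel** (14 × well volume × replicates ÷ 500)
- 50 µL single: 700/500 = 1.4-fold.
- 50 µL duplicate or 100 µL single: 1,400/500 = 2.8-fold.
- 100 µL duplicate: 2,800/500 = 5.6-fold.

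**Unequal dilution.** The plasma is one pool, so volume saved on one analyte serves another. In single 50 µL wells, seven undiluted interleukins take 7 × 50 = 350 µL. The other seven at 1:2.5 take 7 × 20 = 140 µL. The total is 490 µL, which fits with 10 µL to spare.

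**What the 2 mL aliquot holds.** At an assumed haematocrit of 40 to 50%, plasma is 50 to 60% of 2 mL, or 1.0 to 1.2 mL. The plan keeps 500 µL of that. The full amount would cover the 700 µL case undiluted. It would not reach 1,400 µL without a dilution of 1,400/1,200 = 1.2-fold to 1,400/1,000 = 1.4-fold.

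**The case against.** The strongest reply is that the decisive figure is not in the document. The need runs from about 175 µL to 2,800 µL over the assumed range, which straddles 500 µL, and some ordinary combinations fit. Kit-level volumes and dilutions are also what a journal article leaves to the full protocol or a laboratory manual, so their absence is no fault. This stands. A reader might infer that the panel cannot be completed, or that the protocol contains an arithmetic error. Neither follows: no stated volume is contradicted, and the 490 µL example shows that partial dilution can bring even 50 µL single wells within the stored amount.

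A second reply is that cytokines are secondary here. The aims and section 2.2 concern immune-cell biomarkers, no endpoint is a cytokine, and the ROC analysis in section 2.5 is for cell subsets. This also stands and limits the severity.

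A third is that a multiplex format would remove the problem. The protocol does not rule one out, but ELISA with an absorbance readout points to single-plex. Nor can dilution be chosen simply to stretch the sample, because the protocol commits to the manufacturer's instructions.

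A reader might also infer that low-abundance cytokines would fall below detection, with healthy controls worst affected. The protocol gives no concentrations or detection limits, so that cannot be supported from it.

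What survives is the thin margin, the single draw, and the fact that more plasma is already in the tube.

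**Conclusion.** The concern holds as a risk. The protocol itself gives 500 µL for 14 analytes, about 36 µL each. Whether that suffices rests on assumed well volume, replicates and dilution. Undiluted single-plex wells of 50 to 100 µL fall short by 200 µL (700 − 500) to 2,300 µL (2,800 − 500); smaller wells or enough dilution fit, with little or no reserve in the tighter cases. This is a cheap improvement that should be made, held with moderate confidence. It does not threaten the study's main immune-cell aims.

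**What to change.** In section 2.4.1, replace the 500 µL limit with storage of all recoverable plasma from the 2 mL aliquot, in small single-use aliquots. The 1.0 to 1.2 mL figure is what the aliquot contains at the assumed haematocrit; the amount recovered will be somewhat less and should be checked at the bench.

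Then add up the volume required by the chosen kits, including replicates and dead volume. If it exceeds what is stored, either enlarge the plasma aliquot within the same 10 mL draw or use a multiplex assay sized to the stored volume. At a plasma fraction of 50 to 60%, 1,400 µL would need 1.4/0.6 = 2.3 mL to 1.4/0.5 = 2.8 mL of blood, leaving 7.2 to 7.7 mL for cells.

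The article gives a recruitment start (1 January 2023) before its publication date (17 April 2023), so some samples may already be held at 500 µL. For those, set one order of analytes, applied alike in all four cohorts.

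The cost is a few more cryovials and, if the aliquot is enlarged, slightly less blood for cell preparation. No extra blood or participants are needed. Spinning the whole tube before lysis would yield more plasma, but it alters the handling of the cells used for cytometry and sequencing. It should be used only if a pilot check shows that those cells are unaffected.

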#### Preparation of PBMCs

2.4.2.

Venous blood obtained as described in section 2.4.1 will be added to 10 volumes of NH_4_Cl solution and allowed to sit at room temperature for 10 min to lyse the erythrocytes. Samples will be centrifuged at 400 *g* at 4°C for 10 min, the supernatant will be discarded, and the pellet will be resuspended in phosphate-buffered saline (PBS) containing 2% fetal bovine serum. The resuspension will be centrifuged at 400 *g* at 4°C for 10 min again, and the pelleted PBMCs will be resuspended in PBS to a concentration of 2 × 10^6^/mL based on cell counting (33).

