## Introduction

1.

Heatstroke, which can be categorized as classic heatstroke (CHS) or exertional heatstroke (EHS) depending on its cause (1), is the most life-threatening form of hyperthermia (>40.5°C), and it involves central nervous system dysfunction and multi-organ failure (2). Even with intensive care, mortality rates of heatstroke patients can be as high as 30–60% (1, 2). The incidence of heatstroke-related deaths has been increasing globally during the past 2 decades, as record-breaking heatwaves have occurred (1). Heatstroke survivors may experience long-term neurological and cardiovascular complications (1, 2).

Hyperthermia can damage proteins, lipids, and nucleic acids, as well as kill cells directly (3, 4), inducing the production of cytokines to protect against tissue injury (5, 6). If thermoregulation fails to maintain core temperature within an appropriate range, inflammatory responses may become excessive and injure tissue, leading to multi-organ failure and death (7–9), akin to systemic inflammatory response syndrome (SIRS) (10–15). In addition, heatstroke can compromise gastrointestinal integrity, allowing endotoxins and pathogens to enter the circulation and trigger endotoxemia (14). However, potentially informative differences in immune profiles among patients with heatstroke, SIRS, or sepsis have not been fully elucidated.

For lack of a specific biomarker (1), heatstroke is diagnosed based on hyperthermia, history of exposure to extreme heat or vigorous exertion, and alterations of the central nervous system (6, 7). Researchers have undertaken genomic, epigenomic, transcriptomic, proteomic, and metabolomic studies in an effort to identify diagnostic biomarkers (16–18), without much success. The rate of false positive diagnosis of heatstroke remains as high as 24% and the rate of false negative diagnosis as high as 64.5%, especially among patients with atypical symptoms (2). To make matters worse, heatstroke can be difficult to differentiate from sepsis, especially when it involves leukocytosis, which can delay cooling treatments that substantially improve prognosis (1).

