#### Flow cytometry to determine immune cell profiles

2.4.3.

Aliquots of PBMCs (100 μL) will be stained with appropriate antibodies for 30 min at room temperature in the dark in order to label, in separate samples, T lymphocytes, B lymphocytes, monocytes, NK cells, and granulocytes (Table 3). Then samples will be centrifuged at 300 *g* at 4°C for 5 min, the supernatant will be discarded, the pellet will be resuspended in 300 μL PBS, and the suspension will be measured using a FACSLyric ™ flow cytometer (BD Bioscience). The technician performing flow cytometry will be blinded to the origin of the samples.

**Table 3 tab3:** Antibody panels to identify immune cell subsets by flow cytometry.

Fluorophore	Antigen	Fluorophore	Antigen
T cell panel 1		T cell panel 2	
BV421	CD279	BV421	CD279
BV510	CD25	BV510	CD8
BV605	CD45	BV605	CD45
FITC	CCR7	FITC	CD38
PE	CD127	PE	CD69
PerCP-Cy5.5	CD3	PerCP-Cy5.5	CD3
PE-Cy7	CD28	PE-Cy7	CD28
APC	CD45RA	APC	CD45RO
APC-R700	FVS	APC-R700	FVS
APC-Cy7	CD4	APC-Cy7	CD4
B cell panel		Natural killer cell panel	
BV421	CD27	BV421	CD57
BV510	CD19	BV510	CD335
BV605	CD45	BV605	CD45
FITC	CD38	FITC	Lin(CD19/CD14/CD123/CD11C/FC)
PE	IgG	PE	CD127
PerCP-Cy5.5	IgM	PerCP-Cy5.5	CD3
PE-Cy7	CD274	PE-Cy7	CD56
APC	CD80	APC	CD314
APC-R700	FVS	APC-R700	FVS
APC-Cy7	IgD	APC-Cy7	CD16
Monocyte panel		Granulocyte panel	
BV421	CD284	BV421	CD123
BV510	CD40	BV510	CD15
BV605	CD45	BV605	CD45
FITC	CD14	FITC	CD14
PE	HLA-DR	PE	Siglec8
PerCP-Cy5.5	CD80	PerCP-Cy5.5	CD54
PE-Cy7	CD274	PE-Cy7	CD11b
APC	CD163	APC	CD181
APC-R700	FVS	APC-R700	FVS
APC-Cy7	CD16	APC-Cy7	CD64
		BV786	CD16

Flow cytometry data will be analyzed using FlowJo software (Treestar, Ashland, OR, United States), which will be gated to exclude debris, dead cells and doublets but retain single live cells for subsequent analysis. Immune cell subsets will be visualized in two dimensions map using t-distributed stochastic neighbor embedding (t-SNE) (34) and the “uniform manifold approximation and projection” algorithm (UMAP) (35). Then cells will be grouped into phenotypically homogeneous clusters using PhenoGraph (36) or FlowSOM (37), and the clusters will be characterized using Marker Enrichment Modeling (38).

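### Cytometry on a fixed number of cells gives shares, not circulating counts, so a granulocyte-driven leukocytosis can lower main-population shares with no change in those cells

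*Protocol article*

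**What the plan says.** Section 2.4.2 says that venous blood "will be added to 10 volumes of NH_4_Cl solution and allowed to sit at room temperature for 10 min to lyse the erythrocytes". After washing, the pellet is resuspended "to a concentration of 2 × 10^6^/mL based on cell counting". The product is called PBMCs, but no density gradient or other step removes granulocytes, and Table 3 includes a granulocyte panel run on the same preparation.

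Section 2.4.3 continues: "Aliquots of PBMCs (100 μL) will be stained with appropriate antibodies for 30 min at room temperature in the dark". The data are then "gated to exclude debris, dead cells and doublets but retain single live cells for subsequent analysis", mapped with t-SNE and UMAP, and clustered. Counting beads, volumetric counting and absolute counts are not mentioned.

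The Introduction says heatstroke is hard to separate from sepsis "especially when it involves leukocytosis", and states that the profiles of circulating lymphocytes, monocytes, NK cells and granulocytes will be compared. Section 2.5 tests immune cell subsets between cohorts and takes them to ROC curves with Youden cut-offs. It names no comparison with the leukocyte or neutrophil count. Baseline data in section 2.4 include "history of smoking and drinking, family medical history, laboratory results, comorbidities, and treatments"; a blood count is not named and is not tied to the cytometry sample.

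**The concern.** Setting all samples to one concentration is ordinary staining practice. It does mean that the tube no longer carries the donor's leukocyte count. Because granulocytes stay in the suspension, they are part of any denominator made of all live leukocytes, and when they rise every other share of that total must fall.

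The study looks for diagnostic and prognostic immune cell markers in a disease that it says can involve leukocytosis. A lymphocyte, monocyte or NK share could then separate heatstroke from healthy controls and reach a good ROC area while only restating a raised neutrophil count. Section 2.5 as written would not show this. Nor would matching remove it: none of the covariates listed in section 2.1.2 is a leukocyte count.

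**Working it through.** The documents give no figure to reproduce here beyond the laboratory setting, so the check runs from that setting.

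**Cells per tube.** 2 × 10^6/mL (section 2.4.2) × 0.1 mL (section 2.4.3) = 2 × 10^5, the same in every cohort.

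**Share and fold change.** Share = subset count / total leukocyte count (WBC). If the subset's absolute count is equal in two cohorts, the ratio of their shares is WBC of the comparator / WBC of the cases. At equal WBC the ratio is 1 and there is no dilution.

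**Example 1 (assumed, × 10^9/L).** Lymphocytes 2.0 and other non-neutrophil cells 0.5 throughout; only neutrophils change.

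| Neutrophils | Total | Lymphocyte share |
|---|---|---|
| 4 | 6.5 | 2.0/6.5 = 30.8% |
| 12 | 14.5 | 2.0/14.5 = 13.8% |
| 16 | 18.5 | 2.0/18.5 = 10.8% |

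From 4 to 12 the relative fall is 1 − 6.5/14.5 = 55%, with lymphocytes unchanged.

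**Example 2 (assumed, × 10^9/L).** Control WBC 6.0: neutrophils 3.6, lymphocytes without NK cells 1.8, monocytes 0.4, NK cells 0.2. Only neutrophils rise in the cases.

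| Case WBC | Ratio | Lymphocytes (30%) | Monocytes (6.7%) | NK cells (3.3%) |
|---|---|---|---|---|
| 9 | 0.67 | 20% | 4.4% | 2.2% |
| 12 | 0.50 | 15% | 3.3% | 1.7% |
| 15 | 0.40 | 12% | 2.7% | 1.3% |
| 20 | 0.30 | 9% | 2.0% | 1.0% |

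**How often this reaches p < 0.05.** Simulation with 3,000 runs, 40 per cohort, two-sided Mann-Whitney test, Example 2 means, and log-normal counts with an assumed CV of 0.35 for non-granulocytes and 0.40 for neutrophils. Lymphocytes are truly unchanged.

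| Case WBC | Share of all live cells | Absolute count | Share of non-granulocytes |
|---|---|---|---|
| 6.0 | 4.6% | 4.7% | 5.2% |
| 7.5 | 81% | 4.6% | 5.2% |
| 9 | 99.8% | 5.0% | 4.4% |
| 12 | 100% | 4.5% | 5.0% |
| 15 | 100% | 5.6% | 4.4% |

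The last two columns are nominal by construction, since neither quantity contains neutrophils; they show which readouts are safe from this route. A normal approximation on the log scale, with the CV of the share between 0.5 and 0.3, gives 56% to 93% at WBC 7.5 and at least 97% from WBC 9 upward.

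**The case against.** **No passage says that the analysed variable is a share of all live leukocytes.** This stands. Section 2.5 names no denominator, and an article may leave that to a fuller document. The panels carry CD45 as well as lineage markers, so either denominator is possible. The point is therefore conditional. What does not depend on a fuller document is that the fixed input is set here, and that a count not kept with the draw may be impossible to supply later.

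**A reader might infer that circulating numbers are lost for good.** The document does not support that. A pre-dilution count is made, 8 mL of blood is processed (section 2.4.1), and laboratory results are recorded. But the count is used only to set the concentration, cell yield after lysis and washing is not known, and it is not shown that a blood count from the same draw exists in every cohort.

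**A reader might infer that almost every cytometry readout is affected.** It is not. Most panels are lineage-specific, and clusters are characterised by marker enrichment. Within-lineage shares and marker intensity are not diluted by neutrophils. The exposed readouts are main-population shares.

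**A reader might infer that heatstroke versus sepsis is distorted to the same extent.** The figures above describe healthy versus ill. If both diseases raise granulocytes alike, the dilution partly cancels. The documents give no leukocyte counts, so the size for sepsis or bypass cannot be stated.

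**A lower share is a true proportion and may still discriminate.** This is fair. It misleads only when read as fewer cells, or as information beyond the neutrophil count. That is why the added-value check is needed.

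**Conclusion.** The point holds in conditional form. The cytometry as described yields shares of a granulocyte-containing suspension. If main populations are compared as shares of all live leukocytes, a granulocyte-dominated leukocytosis lowers them without any change in the cells: 30.8% to 13.8% in the first example, and a significant difference in about four of five simulated comparisons at a case WBC of only 7.5 against 6.0.

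The sizes rest on assumed counts and CVs. The direction rests on two things only: granulocytes staying in the denominator, which follows from the lysis step and the granulocyte panel, and the rise being mainly granulocytic. A proportional rise in all lineages would leave shares unchanged. The concern is strongest for the contrast with healthy controls and unquantified for sepsis and bypass.

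**What to change.** - **Sections 2.4.2–2.4.3:** Keep the pre-dilution cell count, the suspension volume and the processed blood volume, or take a blood count from the same draw. Report absolute counts (share × total leukocyte count) for the main populations beside the shares. Use within-lineage parent gates for subsets.
- **Section 2.5:** For each candidate marker, show whether it adds to the leukocyte or neutrophil count in the ROC analysis.

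The analysis cost is a multiplication and one extra ROC comparison per marker. The practical cost is a count paired with the draw in every cohort. Baseline laboratory results may not serve: the bypass sample is taken at the end of bypass, and the healthy controls' examination may be up to six months old. Absolute counts bring counting and yield error, and may not be directly comparable for samples taken at the end of bypass, so the shares should stay alongside them.
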